### Plans to give access to the full protocol, participant-level data, and statistical code {31c}

Only researchers directly involved in the project will have access to the full protocol, participant-level data, and statistical code. In case non-recovered participants choose CBT, the treating CBT therapist will have access to the baseline assessment and PROfeel ESM data necessary to determine which treatment modules to provide.

## Oversight and monitoring

### Composition of the coordinating center and trial steering committee {5d}

The Wilhelmina Children’s Hospital, part of UMC Utrecht, is the coordinating center of the present study. The research group running the study day-to-day will meet weekly. Principal investigators will join the meeting monthly. The research group will report study progress to the IRB yearly.

### Composition of the data monitoring committee, its role and reporting structure {21a}

A Data Management Plan (DMP) has been prepared and evaluated by the UMC Utrecht’s data quality management team. Please see section “Data management {19}”.

### Adverse event reporting and harms {22}

This RCT has been appreciated by the IRB as having negligible risk. All adverse events (AE) reported spontaneously by the participant, or observed by the investigator within 2 h of the study visit, will be recorded. All AEs will be followed until they have disappeared, or until a stable situation has been reached. Depending on the adverse event, follow-up may require additional tests or medical procedures as indicated, and/or referral to the general physician or a medical specialist.

All serious adverse events (SAE) resulting in death or life-threatening condition will be reported to the accredited IRB within 7 days of first knowledge, followed by a period of maximally 8 days to complete the initial preliminary report. All other SAEs will be reported within a period of maximum 15 days after the investigator first became aware of the SAE. SAEs need to be followed until the end of study, as defined in the protocol.

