## Introduction

### Background and rationale {6a}

Q-fever is a zoonosis caused by the intracellular gram-negative bacterium *Coxiella burnetii*. Severe chronic fatigue is a frequently reported complaint among patients with a history of Q-fever infection and is described as persistent or recurrent severe fatigue with a profound, debilitating effect on daily life [1, 2]. Especially in children, chronic fatigue affects future well-being and social participation [2, 3]. The most recent Q-fever epidemic took place in The Netherlands from 2007 to 2010 [4]. Since then, up to a dozen of new cases of Q-fever have been confirmed every year [5, 6]. Most of those affected with acute Q-fever recover from fatigue within 6 to 12 months [4]. Approximately 20% does not recover within this timeframe, leading to Q-fever fatigue syndrome (QFS) diagnosis [4, 7]. QFS has been associated with immune deregulation [8] and possibly mitochondrial dysfunction [9]; however, the etiology and pathophysiology of QFS is still largely unknown [8, 9].

The term QFS is derived from chronic fatigue syndrome (CFS), also known as myalgic encephalomyelitis (ME), because of its similar expression. Like with CFS/ME, individuals with QFS have, in addition to severe fatigue, a complex set of symptoms including, e.g., headache, muscle and/or joint strains, sore throat, and painful lymph nodes [6, 7, 10]. Post exertional malaise, unrefreshing sleep, memory or concentration difficulties, and issues regarding mental well-being, are also common [6, 7, 10]. As a result, daily functioning and participation in society are significantly limited [6, 7, 10].

An overlap in symptoms similar to QFS and CFS/ME is also observed in individuals suffering from fatigue in (auto-)immune diseases, such as juvenile idiopathic arthritis (JIA). Previous research has shown that severe fatigue is prevalent among 25% of individuals with pediatric rheumatic diseases [11], which is more prevalent than in the general population [2]. One systematic review reported fatigue among 60–75% of all JIA cases [12], and fatigue has been identified as a long-term sequela in 26% of JIA cases [13].

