### Strategies to improve adherence to interventions {11c}

During the RCT, participants receive a boost from the investigator by phone and/or mail. Participants are also regularly reminded that they can contact the investigator for questions or help with their advice or technical problems with the app.

To improve adherence to the patient-tailored PROfeel lifestyle advices, the advices are formulated clearly and concretely (e.g., “cycle to school 3 days a week to increase physical activity” rather than “increase physical activity”). This way, participants know what is expected of them. Participants receive a weekly survey item on their smartphone, inquiring after their level of compliance.

To improve adherence to the generic dietary advice, participants receive a weekly survey inquiring after their compliance to each aspect of the dietary advice. The surveys function as both monitoring and reminder tools for the participant. Reminders are often used as a tool in behavior change interventions [30], and a meta-analysis has shown that reminders can make a small contribution to behavior change in dietary interventions [34].

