## Data collection and management

### Plans for assessment and collection of outcomes {18a}

The primary outcome of the intervention study is “fatigue severity” as measured by the subscale “fatigue severity” (8 items) of the Checklist Individual Strength-20 (CIS-20). The subscale consists of 8 items (CIS-8). Participants will receive the CIS-8 once a week throughout the study as a survey in the Ethica smartphone app. The weekly CIS-8 has a scoring range of 8–56, with higher scores indicating more fatigue. The CIS-8 has good reliability and discriminative validity [35]. A reduction of 1 standard deviation (SD) is considered clinically relevant.

Secondary outcomes of the intervention study are “quality of life” and “self-efficacy”. Per construct, one VAS item will be added to the weekly CIS-8 questionnaire. In addition, these outcomes will be measured with questionnaires in KLIK, a web-based survey portal (www.hetklikt.nu). “Quality of life” will be measured with the Pediatric Quality of Life Inventory 4.0 Generic Score (PedsQL GCS). This questionnaire consists of four subscales (i.e., physical, emotional, social, and school or work functioning), with total- and subscores ranging from 0 to 100. Higher scores indicate a higher quality of life. The PedsQL GCS has good validity and reliability [36]. An increase of 1 SD is considered clinically relevant. “Self-efficacy” is defined as a sense of control over fatigue symptoms and will be measured with the Self-Efficacy Scale-28 (SES-28). This questionnaire consists of 5 items that inquire about the sense of control related to fatigue, with higher scores indicating more sense of control [37]. An increase of 1 SD will be considered clinically relevant.

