## Discussion

The QFS-study is a comprehensive study examining disrupted biological factors and patient-tailored interventions for fatigued adolescents and young adults with QFS, CFS/ME, or JIA. A few practical or operational issues are expected during the study. The first issue concerns recruitment of QFS participants between the age of 12 and 29 years. As described before, the most recent Q-fever epidemic took place in the Netherlands from 2007 to 2010 [4]. Around that time, the potential youngest participant would have been born. With only a dozen new cases of Q-Fever in The Netherlands per year approximately [5, 6], chances are slim to recruit many young QFS participants. Most QFS participants are expected to be at least 20 years of age, which will be older than most CFS/ME and JIA participants. Not feeling able to balance study or work life with the QFS-study might be a reason for older participants not to participate or to drop-out from the study.

The second issue concerns ESM measurement. During two periods of the study, participants complete ESM measurements approximately five times per day for 4 weeks. Participants might encounter motivation or technical issues during the ESM measurements. The investigator tracks the progress of all participants and takes actions if necessary. To prevent or resolve motivational issues, the investigator explains to the participant why they need to complete the ESM measurement and how many completed surveys are still required. Technical issues with the Ethica app are resolved with the Ethica support team. In case a participant is not able to complete ESM measurement sufficiently due to technical issues, it is possible to restart the ESM measurement period.

The third issue revolves around the behavioral changes imposed in the patient-tailored PROfeel lifestyle and generic dietary advices. The aim of the advices is to give participants insight and autonomy. Hence, the participants act on their advice independently for 12 weeks (unless it is specifically part of the advice to seek guidance). Considering that behavioral change is difficult to impose, the RCT might actually examine which participants are able to independently change behavior and which are not—rather than measuring the effectiveness of the advices itself. The implemented *N*=1 design will be a strength of the study in this aspect.

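### Adverse events are collected only passively over two 12-week periods without a visit, so non-serious events are likely to be under-recorded and hard to compare by arm

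*Protocol article*

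**What the plan says.** The section on adverse events and harms states: "All adverse events (AE) reported spontaneously by the participant, or observed by the investigator within 2 h of the study visit, will be recorded". The sentence before it gives the context: "This RCT has been appreciated by the IRB as having negligible risk". The article describes no routine question about adverse events. Serious events have their own reporting timelines and are not the subject of this point.

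The Discussion says of the interventions: "Hence, the participants act on their advice independently for 12 weeks", with an exception where seeking guidance is itself part of the advice. In Table 1 the only visits around the intervention periods are T1 and T2 for the first and T3 and T4 for the second. Contact in between is described as follows: "During the RCT, participants receive a boost from the investigator by phone and/or mail". Participants are also reminded that they may get in touch about their advice or the app.

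In its account of QFS and CFS/ME the Background says: "Post exertional malaise, unrefreshing sleep, memory or concentration difficulties, and issues regarding mental well-being, are also common". The adherence section illustrates a concretely worded PROfeel advice with "cycle to school 3 days a week to increase physical activity".

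For the primary outcome, the outcome section sets a one-sided threshold: "A reduction of 1 standard deviation (SD) is considered clinically relevant". For quality of life and self-efficacy the threshold is likewise 1 SD in the direction of benefit.

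**The concern.** A 2 h observation window suits an acute reaction at a visit, such as one to blood sampling. It does not suit an advice whose effects, good or bad, build up at home over weeks. In that time an event enters the record only if the participant decides to mention it. A brief flare that has settled by the next visit is easily left out, particularly in patients who are used to fluctuating symptoms.

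Two things are at stake. A low count of adverse events would be hard to interpret, because few events and few reports look alike. A difference between arms would be hard to interpret too, because participants know their allocation and nothing ensures that both arms are asked the same question.

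**Working it through.** The plan states no adverse event rate and no capture rate, so there is no figure to reproduce. What follows is the share of time under observation, then an illustration under assumed rates, then a comparison of sections.

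**1. Share of a period open to investigator observation.** Inputs: 12 weeks per intervention (Table 1); 2 h per visit (harms section); one visit at each end.

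- Length of a period: 12 × 7 × 24 = 2,016 h
- Observation windows: 2 × 2 = 4 h
- Share: 4 / 2,016 = 0.2%

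This figure covers the observation route only. Spontaneous reports have no stated time limit.

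**2. What passive capture can do to a count.** Inputs: 60 participants randomised 1:1, so 30 per arm. Assumptions, not in the document: a share *p* of participants has an event, and each such event is recorded with probability *c*. Then the expected number recorded is 30*pc*, and the chance that none is recorded is (1 − *pc*)^30.

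| *p* | *c* | expected recorded | chance of none |
|---|---|---|---|
| 10% | 1 | 3.0 | 4% |
| 10% | 0.5 | 1.5 | 21% |
| 10% | 0.25 | 0.75 | 47% |
| 20% | 1 | 6.0 | 0.1% |
| 20% | 0.5 | 3.0 | 4% |
| 20% | 0.25 | 1.5 | 21% |
| 30% | 1 | 9.0 | <0.1% |
| 30% | 0.5 | 4.5 | 0.8% |
| 30% | 0.25 | 2.25 | 10% |

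The table shows the mechanism and a range. It does not estimate what happens in this trial.

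**3. Unequal capture.** With a true risk of 20% in both arms and assumed capture of 0.3 and 0.5, the expected counts are 30 × 0.2 × 0.3 = 1.8 and 30 × 0.2 × 0.5 = 3.0. With equal capture they coincide. The document does not say which case applies.

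**4. Do other data fill the gap?** Largely, for sustained worsening:

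- The CIS-8 and one VAS item each for quality of life and self-efficacy are collected weekly in both arms.
- KLIK adds the PedsQL, pain, and anxiety and depression scales at T0 to T4.
- Each participant is analysed individually with the permutation distancing test.

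But the article does not put these data to use for harm. The 1 SD threshold runs only towards benefit. The pain and mood scales are listed as possible predictors, mediators or moderators. The group-level tests compare means. The section on additional analyses says there are none. A count of worsened participants by arm appears nowhere.

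**The case against.** The strongest defence is proportionality. The ethics board rated the trial as negligible risk, the interventions are advice, and light collection of adverse events is a legitimate choice in that setting. Spontaneous reports are accepted at any time, the investigator makes contact during each period, T2 and T4 include an evaluation of the intervention, and a monitor inspects adverse event reports. The article condenses a full protocol that may specify questioning at visits. All of this stands, and it makes the point an improvement rather than an error. It does not remove the point: neither the contacts nor the evaluations are described as asking about adverse events, and a risk rating given in advance cannot be checked with passive data.

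Three stronger readings are tempting, and the document does not support them.

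- *Harm by arm will be missed.* Sustained worsening of fatigue, pain, mood or quality of life would be visible in scales that both arms complete. The gap is narrower: short flares, events outside those scales, and the lack of a summary.
- *Differences in adverse events will reflect contact frequency.* This is possible but not shown. The investigator's boost is worded identically for both interventions. The documented differences are an additional weekly diet-compliance survey, and fatigue care that is permitted only within a PROfeel advice. Neither is shown to prompt reports to the investigator.
- *The trial cannot tell no benefit from a mixture of benefit and harm.* The individual-level objective and its weekly data are designed to look at exactly this.

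The clinical premise also has limits. Post-exertional malaise is called common for QFS and CFS/ME, which make up 40 of the 60 participants; for JIA only an overlap in symptoms is stated. The cycling example illustrates clear wording, and advices are agreed with the participant with feasibility in mind.

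**Conclusion.** The point holds in a limited form. Ascertainment of adverse events is passive across two 12-week periods, so non-serious events are likely to be under-recorded and counts by arm will be hard to compare. Observation covers about 0.2% of a period. How many events would be lost, and whether the arms would differ in reporting, cannot be established from the document; every rate in the illustration is an assumption. Sustained worsening is measured but is neither defined nor summarised by arm. The conclusion rests on the article as published and would weaken if the full protocol already requires an adverse event question at visits. It is a cheap improvement and does not affect the primary analysis.

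**What to change.** In the section on adverse events and harms, add that every participant is asked one identically worded open question about new or worsened health problems at T2, T3 and T4. The same item could optionally go into the existing weekly Ethica survey.

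In the outcome and statistical methods sections, mirror the threshold. Report by arm the number of participants whose CIS-8 rises, or whose PedsQL generic core score falls, by at least 1 SD from T1 to T2, alongside the number who improve by at least 1 SD. Use the same SD in both directions, and state how many in each arm have no T2 value, since data of drop-outs are analysed only up to the point of leaving.

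One limit should be stated with the count. The CIS-8 ends at 56 and entry requires more than 39 (QFS, CFS/ME) or more than 34 (JIA). A participant at the lowest qualifying whole score can therefore rise by at most 56 − 40 = 16 or 56 − 35 = 21 points, and others by less. The PedsQL count guards against reading a ceiling as absence of worsening.

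The cost is more background non-serious events to log, especially if the weekly item is used in patients with fluctuating symptoms, and a higher reported event count. The worsening count needs no new data, so it can be added even if collection is well advanced.

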### Frequency and plans for auditing trial conduct {23}

The QFS-study will be followed by an internal monitor at UMC Utrecht. The monitor is independent from investigators and sponsor. In accordance with the monitor plan, his or her first visit will take place after 3 to 5 inclusions. Afterwards, the monitor will visit annually. During monitor visits, the monitor will inspect the Investigator Site File, informed consents, adherence to study protocol, (S)AE reports, and data safety. Inspection outcomes will be recorded, and required actions and follow-up will be documented in the Monitoring Issues and Action Tracker by the monitor.

### Plans for communicating important protocol amendments to relevant parties (e.g., trial participants, ethical committees) {25}

Amendments are changes made to the research protocol, after the IRB of the University Medical Centre Utrecht has given a positive opinion. The IRB at UMC Utrecht has a standardized procedure for this. The investigator is responsible for submitting an amendment. When an amendment is final, all parties involved will be informed of this by the investigator through written and oral communication.

### Dissemination plans {31a}

The research data will be disclosed unreservedly and reported in accordance with the principles of good clinical practice. Public disclosure will be accomplished by publication of the results in scientific peer-reviewed journals, (poster) presentations during (inter)national conferences, workshops, and the writing of a PhD thesis. Results of this study will be communicated to patient organizations through personal communications, meetings (considering their participation in this project), websites, letters, and/or symposia.

## Discussion

The QFS-study is a comprehensive study examining disrupted biological factors and patient-tailored interventions for fatigued adolescents and young adults with QFS, CFS/ME, or JIA. A few practical or operational issues are expected during the study. The first issue concerns recruitment of QFS participants between the age of 12 and 29 years. As described before, the most recent Q-fever epidemic took place in the Netherlands from 2007 to 2010 [4]. Around that time, the potential youngest participant would have been born. With only a dozen new cases of Q-Fever in The Netherlands per year approximately [5, 6], chances are slim to recruit many young QFS participants. Most QFS participants are expected to be at least 20 years of age, which will be older than most CFS/ME and JIA participants. Not feeling able to balance study or work life with the QFS-study might be a reason for older participants not to participate or to drop-out from the study.

The second issue concerns ESM measurement. During two periods of the study, participants complete ESM measurements approximately five times per day for 4 weeks. Participants might encounter motivation or technical issues during the ESM measurements. The investigator tracks the progress of all participants and takes actions if necessary. To prevent or resolve motivational issues, the investigator explains to the participant why they need to complete the ESM measurement and how many completed surveys are still required. Technical issues with the Ethica app are resolved with the Ethica support team. In case a participant is not able to complete ESM measurement sufficiently due to technical issues, it is possible to restart the ESM measurement period.

The third issue revolves around the behavioral changes imposed in the patient-tailored PROfeel lifestyle and generic dietary advices. The aim of the advices is to give participants insight and autonomy. Hence, the participants act on their advice independently for 12 weeks (unless it is specifically part of the advice to seek guidance). Considering that behavioral change is difficult to impose, the RCT might actually examine which participants are able to independently change behavior and which are not—rather than measuring the effectiveness of the advices itself. The implemented *N*=1 design will be a strength of the study in this aspect.

The last issue concerns healthy control recruitment. We aim to recruit up to 80 healthy controls. We foresee difficulty in finding enough healthy adolescents and young adults willing to participate, especially if they are not familiar with Q-fever and QFS. Therefore, we aim to recruit as many siblings and friends of QFS participants as possible. This strategy might also increase the likelihood of recruiting healthy controls with seropositive *Coxiella burnetii* status. If needed, we will also recruit as many siblings and friends of CFS/ME and JIA-participants as possible and share calls for participation online. We aim to recruit up to 80 healthy controls, to facilitate matching for age and gender in the biological objectives of the QFS-study.

Ultimately, the QFS-study aims to contribute to unraveling disrupted biological factors in QFS and further development of (personalized) treatments for chronic fatigue in adolescents and young adults.

## Trial status

The QFS-study has been described according to version 6 of the study protocol, approved by the IRB of UMC Utrecht on March 25, 2021. The first version of the study protocol received approval from the IRB on June 16, 2020, after which recruitment began in January 2021. Data collection is expected to be completed in December 2022. The QFS-study has been registered at www.trialregister.nl as Trial NL8789 on July 21, 2020.

## Data Availability

Only researchers directly involved in the project are allowed to access the final trial dataset. In case a non-recovered participant chooses CBT as post-trial care, the treating CBT therapist is allowed to access that participant’s baseline assessment and PROfeel ESM data if this is necessary to determine which treatment modules should be provided.

